**Method:**

SMART-AGE examines the effect of an app-based multilevel treatment designed to enhance social participation, physical fitness, and health awareness. The target population comprises healthy and community-dwelling adults 67 years and older with basic digital skills in two socially diverse communities. Treatment relies on an Android-based tablet computer, on which three apps offering interventions in the core areas of social participation, physical fitness, and health awareness are pre-installed. A feedback app designed to provide participants with a feedback option at any time is also offered. Participants are randomly assigned to three intervention arms and assessed at baseline and after 3 and 6 months. Arm 1 receives the full intervention, consisting of the social participation app, the physical fitness app, the health awareness app, and the feedback app. The health awareness app is available in months 4 to 6, meaning that participants receive the full three-app intervention only in the second half of the intervention period. Arm 2 receives the social participation app and the feedback app throughout the intervention. Arm 3 serves as an active control condition in that a stand-alone tablet with a low-dose introduction to publicly available standard apps is provided. The data protocol includes assessment of three primary outcome domains: social support and loneliness, motor capacity and physical performance, and health awareness and health locus of control. Potential moderators (e.g., cognitive function, depression) as well as various technology-oriented constructs (e.g., skills, acceptance) are also assessed. App use data are automatically collected across the full intervention interval in arms 1 and 2. Data management is conducted within a cloud-based REDCap architecture. Feedback recordings via the feedback app are collected in arms 1 and 2 and undergo qualitative analysis.

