### Sample size

The sample size was determined through an a-priori power analysis to ensure adequate power for the planned structural equation modeling analyses. We will study the effect of the intervention groups as contrasted with the active control condition on main outcomes using latent change models, in which each of the four main outcome domains will be represented in latent space by at least three manifest variables. Assuming measurement invariance across the three study time points, the two intervention sites, and the two experimental groups and one active control group, this results in a model with 128 estimated parameters and 16,162 degrees of freedom. With the requirement of five participants per estimated parameter, an expected dropout rate of 10% and a further increase to balance the strata, we plan to collect a sample of 720 participants to be analyzed based on an intention-to-treat analysis, that is, all participants having entered the study at baseline will become part of the statistical effect analysis independent of their “fate” along the full observational period. Moreover, at each of the three study time points for each of the three groups, the planned sample size meets Browne and Cudeck’s [57] recommendations for model testing based on the close fit hypothesis (H0, ε ≤ 0.05; H1, ε ≥ 0.08; *α* = 0.05) using the root mean square error of approximation (RMSEA; 44). This provides a statistical power of 1 – *β* > 0.99 for the main model across all study time points as well as for analyses conducted at a single time point, ensuring that the study has sufficient power to reject the model if its fit to the empirical data is inadequate.

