### Blinding

Participants are always aware of the study arm they are assigned to, as they either have access to none, two, or all four of the project apps, except during the baseline assessment. To gather data, two HVs, HV I and HV V, are conducted. It is crucial that the researchers conducting these visits remain blinded to the participants’ group assignments. To facilitate this, the research team is divided into two distinct groups: assessors and app-instructors. The assessors are responsible for data collection during HV I and HV V, while the app-instructors handle HV I, II, III, and IV. The initial HV occurs prior to the randomization of participants, allowing both assessors and instructors to be involved in this stage of the study. We do not anticipate any requirement for unblinding the assessors, but if required, the project coordinators will have access to group allocations and any unblinding will be reported. The randomization list used to allocate participants to the study arms was created by the lead study statistician and the project coordination team, who are the only ones with access to the data file containing personalized information. After individuals are screened positive, the project coordination allocates them to the randomly selected study arm using a study management software. The software allows the information of the allocated study arms to be hidden from blinded assessors while showing it to user groups who need this information.

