### Statistical methods

Our main hypotheses will be tested using multilevel and structural equation models, following an intention-to-treat analysis. We will test the effect of experimental group on primary outcomes separately for each outcome with a 3 × 3 factorial design multilevel model with the between-subjects factor *study arm* (active CG vs. partial IG vs. full IG) and the within-subjects factors *study time point* (study start vs. 3 months vs. 6 months), followed by post-hoc comparisons controlling for the family-wise error rate. Models will include random intercepts for each participant and their place of residence. As covariates, we will consider participants’ gender, their age, and their frequency and intensity of app usage. We plan to report all analyses with and without the inclusion of these covariates. Where the assessment of primary outcomes is only possible during HVs, we will remove the 3-months level from the within-subjects factor *study time point*.

In addition, we will test the effect of experimental groups on primary outcomes first separately for each outcome and then jointly for all four primary outcomes using latent change models. In these models, the multilevel structure of the data will be accounted for by multigroup comparisons to examine whether (a) the effects of the two IGs are larger than the effects of the active CG (see hypotheses), whether (b) the effects of the full IG are larger than the effects of the partial IG (see hypotheses), and (c) by which individual and/or sociodemographic variables the effects of the two interventions on the four primary outcome variables are moderated.

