For all statistical tests, we will use alpha = 0.05 as the threshold for statistical significance. Post-hoc comparisons will be controlled for the family-wise error rate. We will be reporting standardized effect sizes and confidence intervals whenever possible. In addition, we will evaluate the goodness-of-fit of SEMs based on the comparative fit index [CFI; [59]] and the root mean square error of approximation [RMSEA; [39]] and compare model fits with the Akaike Information Criterion [AIC; [60]] and the likelihood ratio test. Following the recommendations by Browne and Cudeck [58] and Hu and Bentler [61], we consider CFI values > 0.90 and RMSEA values < 0.08 to indicate acceptable model fit and CFI values > 0.95 and RMSEA values < 0.06 to indicate good model fit. AIC differences ≥ 10 will be interpreted to indicate a substantial advantage in relative model fit in direct model comparisons [62]. We will assess the statistical significance of model parameters with the two-sided critical ratio test. To our knowledge, this is the first study to systematically monitor and evaluate long-term app usage in a German sample of older adults. We therefore lack the necessary prior knowledge to determine exclusion criteria for app usage and engagement with the tablet. Thus, a blinded analyst [63] will screen study partners’ app usage after the data is collected to propose appropriate criteria. The blinded analyst will not have access to the outcome variables, protecting the confirmatory nature of the statistical inference.

Outlier values in measured variables (assessments) will be removed if they exceed ± 3 SD of the sample mean of their respective study arm and study time point. In addition, we will exclude individuals whose responses appear random (e.g., identical responses to all questions). Physical activity data will only be included if the individual has worn the sensor for at least 4 days.

The type of missing data will be assessed and accounted for using the full information maximum likelihood method in all statistical models. If data are found to be Not Missing at Random, this will be addressed appropriately to minimize potential bias and stated as a limitation.

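### Usage-based exclusion criteria, to be proposed after data collection, are not reconciled with the stated intention-to-treat analysis, and hiding outcomes from the analyst does not remove selection bias

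*Protocol article*

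**What the plan says.** Two sections of the protocol article set the analysis principle. Sample size says that "all participants having entered the study at baseline will become part of the statistical effect analysis independent of their “fate” along the full observational period". Statistical methods opens with "Our main hypotheses will be tested using multilevel and structural equation models, following an intention-to-treat analysis".

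Later in Statistical methods, the article explains that there is no precedent for long-term app monitoring in this population, and continues: "We therefore lack the necessary prior knowledge to determine exclusion criteria for app usage and engagement with the tablet". The remedy is that "a blinded analyst [63] will screen study partners’ app usage after the data is collected to propose appropriate criteria". The safeguard offered is this: "The blinded analyst will not have access to the outcome variables, protecting the confirmatory nature of the statistical inference". The article does not say which analysis the criteria will define. It describes no per-protocol, complier or sensitivity population.

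On where usage is recorded, the Method part of the Abstract says: "App use data are automatically collected across the full intervention interval in arms 1 and 2". Participant timeline reads differently: at the first home visit, before randomisation, the tablet is put into a mode that lets app use be monitored from then on, with no restriction by arm. Blinding describes participants as knowing their arm, "as they either have access to none, two, or all four of the project apps".

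**The concern.** A participant who stops using the apps stays in the analysis under the Sample size section and may be removed under the later part of Statistical methods. Both rules cannot govern the same tests.

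Usage is behaviour after randomisation. It also means something different in each arm, because the arms are offered different apps. People who stop using an app may differ in mood, cognition, health or motivation from those who continue. If they are removed from an intervention arm and no equivalent group is removed from the control arm, the arms no longer differ by chance and treatment alone.

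Keeping the analyst away from outcomes solves another problem: it stops anyone choosing a cut-off because of the result it gives. A cut-off chosen in complete ignorance of outcomes still selects on a variable that may be related to them. At stake is whether a reported benefit could be partly or wholly a product of selection.

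**Working it through.** **1. The plan's own sample size.** 128 parameters × 5 participants = 640. Allowing for 10% dropout, 640 / 0.90 = 711.1, so 712. The next multiple of 72 (the unit given under Recruitment) is 720, or 240 per arm, as stated. After 10% dropout, 240 × 0.90 = 216 per arm and 648 in total, only 8 above the plan's minimum of 640. Removing 10% of both intervention arms as randomised would cost 2 × 24 = 48 people.

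**2. Inputs for the bias.** From the article: 216 per arm (derived above) and two-sided alpha 0.05. Not in the article, hence assumed:
- excluded share e, 5% to 30%;
- correlation rho of usage with the follow-up outcome, 0.1 to 0.3;
- the excluded are the lowest users of one intervention arm, with the control arm left whole;
- no true effect, and a 1.96 cut-off without multiplicity adjustment.

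**3. Follow-up-only comparison.** With q the e-quantile of the standard normal and φ its density:

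bias = rho × φ(q) / (1 − e), SE = √[1 / (216(1 − e)) + 1/216]

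Example, e = 20%, rho = 0.2: φ(q) = 0.280; 0.280 / 0.80 = 0.350; bias = 0.2 × 0.350 = 0.070 SD. SE = 0.102, ratio 0.69, two-sided rejection rate 10.5%.

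| e | rho | bias (SD) | type I error |
|---|---|---|---|
| 5% | 0.1 | 0.011 | 5.1% |
| 10% | 0.2 | 0.039 | 6.8% |
| 10% | 0.3 | 0.058 | 9.1% |
| 20% | 0.2 | 0.070 | 10.5% |
| 20% | 0.3 | 0.105 | 17.7% |
| 30% | 0.3 | 0.149 | 29% |

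Simulation with 20,000 replicates agrees: 0.071 SD and 10.9% for the fourth row, 0.149 SD and 30.3% for the last.

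**4. Full against partial intervention.** If share e is removed from the full arm and e/2 from the partial arm, the spurious difference runs from 0.005 SD (e = 5%, rho = 0.1) to 0.067 SD (e = 30%, rho = 0.3). It vanishes if selection is the same in both.

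**5. Change-type analysis.** The planned models use baseline (arm by time, and latent change), so what counts is how usage relates to change. Let k be the ratio of the baseline correlation to the follow-up correlation, and assume a pre-post correlation of 0.7:

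bias in change = (1 − k) × rho × φ(q) / (1 − e), SD of change = √[2(1 − 0.7)] = 0.775

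Simulated change scores, for (e, rho) = (20%, 0.2), (20%, 0.3) and (30%, 0.3):

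| usage relates to | bias (SD of outcome) | type I error |
|---|---|---|
| baseline and follow-up equally (k = 1) | about 0 | about 5% |
| baseline at 70% of follow-up (k = 0.7) | 0.02, 0.03, 0.04 | 6% to 9% |
| follow-up only, so change alone (k = 0) | 0.07, 0.11, 0.15 | 15% to 46% |

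**The case against.** The strongest reply is that the article states intention-to-treat twice and nowhere says that usage criteria will be applied to the confirmatory tests. The analyst only proposes criteria. The article also plans analyses for which a minimum-usage rule would be natural: the exploratory dose-response question under the hypotheses, and the linking of usage patterns to outcome change under Outcomes. This stands in part. That the exclusions enter the confirmatory analysis is an inference and not stated text. It is a strong one, because the procedure is defended by reference to confirmatory inference and no other analysis set is named.

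Three further readings are tempting and go too far.
- A reader might infer that controls can never be excluded. The Abstract limits app-use data to arms 1 and 2, but Participant timeline suggests monitoring of all tablets, the criteria also cover engagement with the tablet, and app usage is listed as a covariate in the three-arm model. Controls might have some engagement record. It would still not be the counterpart of using an intervention app.
- A reader might assume that low users are the ones to go. That is plausible, but the article does not say so.
- A reader might take the 10% to 29% error rates as the expected damage. They belong to a follow-up-only comparison at the upper end of assumed inputs. Where usage reflects stable traits already present at baseline, the planned models largely cancel the bias. The article's family-wise control of post-hoc comparisons would also lower these rates.

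A missing definition of analysis sets could be left to an unseen analysis plan. Here the difficulty is in what the article itself says: two rules that conflict if applied to the same tests, and a safeguard credited with more than it can do.

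**Conclusion.** The concern holds as an unreconciled conflict between full intention-to-treat and usage-based exclusions set after data collection. The claim that outcome blinding protects the confirmatory inference is incomplete, since it covers the choice of cut-off but not selection on a post-randomisation variable. Each of the three arm contrasts includes at least one arm with usage data, so each can be affected.

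The size cannot be fixed from the article. Under the assumptions above, it runs from negligible (0.011 SD, 5.1% type I error) to 0.149 SD and 29% in a follow-up-only comparison. The latter is close to the d = 0.17 for loneliness that the article cites from the earlier PRISM trial. In change-type models it runs from about zero to 0.15 SD and 46% across the three scenarios tested, depending on whether usage predicts change. Nothing in the article caps the share excluded. Because the rule decides who enters the comparison, it should be settled before outcomes are analysed.

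**What to change.** Add to Statistical methods that no randomised participant is excluded from any confirmatory analysis because of app usage or tablet engagement. State that the blinded analyst's criteria define only a supplementary analysis, labelled per-protocol or complier-average (with randomisation as the instrument), and that they are fixed before usage data are linked to outcomes. Reconcile the Abstract with Participant timeline on whether usage is recorded in the control arm, so that the supplementary set can be defined for all arms.

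The cost is a few sentences. The planned 720 participants (240 per arm) and the two-sided 5% level are unchanged, no new data are needed, and usage-restricted results move to supplementary status. If the sponsor always meant the criteria as supplementary, the same wording resolves the conflict.

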## Methods: monitoring

### Data monitoring committee

A study management group (SMG) was created with representatives of all field-relevant work packages including the project coordinators, statisticians, data managers, app administrators, and assessors. The SMG meets biweekly to supervise the incoming data flow and discuss upcoming problems in the data collection.

### Trial monitoring

There are no regularly scheduled Ethics Committee meetings, as the trial is considered a low-risk intervention. Eventual changes to the protocol in rare cases are initially discussed within the SMG and in cases also with the consortium. In some cases, advisory board members are also involved. If needed, issues and needs for (minor) adjustments are communicated to the ethics committee and the German Clinical Trials Register via an amendment.

### Harms and participant retention

All potential adverse events are systematically recorded by the project coordination. An adverse event is defined as any period of illness, hospitalization, or falls, regardless of the suspected cause. If clarification is required, medical questions will be forwarded to a study doctor. These reports are then reviewed by an independent safety monitor. SPs receive a tablet when they enter the survey, which they keep after study completion as an incentive. All study participants also receive individual feedback on selected measured areas. If an SP deviates from the study protocol or discontinues the study, the reasons for this are strictly documented using a specifically designed study management tool that also serves, for example, for documenting the screening procedure.

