### Digital strategies for enhancing physical activity

Besides its most important role for social participation, enhanced physical fitness in later life comes with multi-level positive effects on various health domains (e.g., cardio-vascular, cognitive), maintenance of functional independence, as well as supporting fall prevention [20, 21]. Meanwhile, a range of reviews and meta-analyses showed that app-based mobile interventions are effective and highly promising for altering physical fitness and activity [22–24]. Additionally, digital apps contribute to improving accessibility, scalability, cost-effectiveness, and equity in healthcare [25]. A prime example is the app Keep On Keep Up (KOKU). Previous studies on KOKU demonstrated that users found the program appealing, motivating, and entertaining after 6 weeks of independent and unsupervised usage [26]. SMART-AGE also considers the evaluative studies conducted by Daniels et al. [27] and van Het Reve et al. [28]. In the SMART-AGE study, a German version of KOKU is used.

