### Participant timeline

Home-based assessments take place at the time of study enrollment (T1) and after 6 months (T6). In addition, a brief online self-assessment will be conducted 3 months after study enrollment (T3). At the beginning of the first home visit (HV; day 1 in T1), participants are informed about data protection, can ask open questions, and get general information about the study. Then they are provided with a tablet, a corresponding manual, and are instructed on how to use the tablet in a short training session. At that moment, the tablet is switched to “study mode,” enabling the monitoring of app usage data of the participants from that point forward. Afterwards the online-assessments are explained and set up on the tablet. Then the home-based assessments take place including cognitive and motoric measurements. During the motor capacity assessment, the body-fixed movement sensor is placed on the participant’s lower back.

One week after the initial HV, the randomization has already taken place, and a second HV is conducted for participants of all groups. During this visit, the tablets are modified allowing participants in both IGs (arms 1 and 2) access to two SMART-AGE specific apps: smartVERNETZT and smartFEEDBACK. These groups also receive instructions and a manual on how to use these new apps. Participants in the CG (arm 3) are given access to the standard applications on the tablet. However, detailed explanations are only given for the video chat tool. The documents containing information about the SPs, completed and signed during the HVs, as well as the data sheets of the cognitive test battery, are securely stored in a locked cabinet in SMART-AGE designated office spaces. Four to 6 weeks after the second HV, participants in the full IG additionally receive access to and are instructed in the use of the KOKU app. Approximately 10 days after the digital assessment at 3 months, the participants of the full IG are introduced to the smartIMPULS app during HV IV.

In order to counterbalance potential social activation effects, 25% of participants in study arms 2 and 3 (active CG and the partial IG) were randomly selected to receive one additional video calls. Randomization was performed using the R package “blockrand” [39].

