smartVERNETZT	– Weekly news on findings on physical activity, technology, social participation and local events – Integrated tools: calendar, address book, camera, notes, clock, calculator, Internet browser and games are included – Provides links to health websites, local counseling services, digital literacy resources, cognitive attention games, analog exercise programs, activities and offers (e.g., group meetings, volunteering), and local educational programs – Allows social networking through e-mail, social networks, and video chat
KOKU	– Progressively structuredtraining program comprising seven levels, each lasting a minimum of 2 weeks. Each week includes 3 training days, with three exercises per day; Green check marks indicate progress – Gamified training with an interactive avatar, demonstrating 26 strength and balance exercises (with goals description and safety instructions), based on evidence-based fall-prevention programs (Otago, FaME [46, 47]) – Users provide feedback on physical exertion; based on this training progression is automatically adjusted – Four health literacy games on home safety, bone health, nutrition and hydration
smartIMPULS	– Daily prompts with one to four questions addressing current life, functioning in daily life tasks and health situations – Addresses the following health domains: nutrition, activities of daily living, mobility, social participation, cognitive functioning, physical functioning, psychological factors, preventive health check-ups, pain, fear of falling, perceived stress, hearing ability, and vision – Questions repeat at set intervals based on expected changes in each domain; unanswered questions accumulate but can be skipped – Supports attention to specific health domains by giving hints based on user responses – Hints suggest follow-up actions (e.g., doctor visit, counseling) or offer additional information – Provides an overview of given answers, filterable by health domains and received hints, including status indicators (new, postponed, completed)
smartFEEDBACK	– Allows users to provide feedback on app use and usability issues at any time – Supports both explicit and implicit feedback, either voluntarily submitted (push) or prompted by the system (pull) – Up to five feedback questions per day (pull); all questions can be skipped

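### The adverse-event definition does not name injury, pain or dizziness without a fall, so exercise harms are likely to be under-recorded in the only arm that receives the KOKU training

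*Protocol article*

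**What the plan says.** The section on harms and participant retention sets the recording rule, "All potential adverse events are systematically recorded by the project coordination", and then defines the term: "An adverse event is defined as any period of illness, hospitalization, or falls, regardless of the suspected cause". Medical questions go to a study doctor if something needs clarifying, and "These reports are then reviewed by an independent safety monitor". Reasons for deviating from the protocol or discontinuing are documented in a study management tool, which is described apart from the adverse-event reports.

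Table 1 (Intervention section) describes KOKU as a progressive programme with an avatar "demonstrating 26 strength and balance exercises (with goals description and safety instructions". On frequency it says "Each week includes 3 training days, with three exercises per day", and on progression "Users provide feedback on physical exertion; based on this training progression is automatically adjusted". According to the participant timeline, four to six weeks after the second home visit "participants in the full IG additionally receive access to and are instructed in the use of the KOKU app". The hypotheses confirm that neither the partial intervention arm nor the active control has KOKU.

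**The concern.** The definition and the intervention do not fit each other. A cold in any arm is an adverse event. A pulled muscle from an exercise in the full arm, treated at home, is not clearly one. Table 1 itself recognises a physical risk, because it lists safety instructions and exertion feedback that steers progression. Of the harms that such training could plausibly cause in people aged 67 and over, the definition names only falls.

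The independent safety monitor reviews the reports that the definition generates. If those reports consist mainly of intercurrent illness, which is common to all arms, and contain few exercise injuries, any later statement about the safety of the full package rests on events that were not looked for. The article calls the trial low-risk (trial monitoring section), and these data could hardly test that for exercise injury.

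**Working it through.** **1. The definition set against plausible events**

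- A fall, during exercise or not: counted.
- Strain, pain or dizziness leading to admission: counted as hospitalization.
- Back pain that lays someone up for some days: counted only if the recorder reads it as a period of illness.
- Strain, joint pain or dizziness managed at home, participant carries on: no clear place.
- The same, but the participant stops: documented as a reason for deviation or discontinuation, a route not described as reaching the safety monitor.
- A cold, in any arm: counted.

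The unclear cases are those most tied to KOKU, and KOKU is in one arm only.

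**2. Exposure (an upper bound, not a harm count)**

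The plan gives no harm figure to reproduce. The arm size used below does reproduce: 128 parameters x 5 = 640; 640 / 0.90 = 711.1, so 712; the next multiple of 72 is 720, or 240 per arm.

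The second home visit is one week after the first, so KOKU opens at about weeks 5 to 7. With T6 at about week 26, 19 to 21 weeks remain. At 3 days x 3 exercises per week, that is 19 x 9 = 171 to 21 x 9 = 189 exercise performances per fully adherent participant. The seven levels at their two-week minimum give 14 x 9 = 126. For 240 participants the maximum is 240 x 171 = 41,040 to 240 x 189 = 45,360. This assumes full adherence and no dropout, whereas the plan expects 10% dropout.

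**3. How much of an excess would be seen**

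The documents give none of these three inputs, so all are assumptions:

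- p0: share of participants with a counted event in the background;
- x: excess share with a non-fall exercise injury in the full arm;
- c: share of those injuries that is counted as illness or hospitalization.

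Counted difference = c * x * (1 - p0), with injuries independent of background events.

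For p0 = 20% and x = 10% this is c * 0.10 * 0.80 = 0.08c:

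- c = 1: 8 points (240 x 0.08 = 19.2 participants)
- c = 0.5: 4 points
- c = 0.25: 2 points (240 x 0.02 = 4.8 participants)
- c = 0: 0 points

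For x from 5% to 15% and p0 from 20% to 40%, the difference with all injuries counted runs from 0.05 x 0.60 = 3 points to 0.15 x 0.80 = 12 points. With a quarter counted it runs from 0.75 to 3 points.

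If the arms were compared at 240 each, two-sided alpha 0.05, power would be about 54% for 8 points, 18% for 4 and 8% for 2. Complete recording therefore serves mainly to describe harm, not to test it.

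**4. Direction of the error**

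Suppose KOKU lowered the share with a fall from 20% to 16%, and a further 10% of the full arm had only an uncounted injury. The counted difference is 16 - 20 = -4 points; the full difference is 16 + 10 - 20 = +6 points. If injuries overlap with falls independently, as in step 3, it is 16 + 10 x 0.84 - 20 = +4.4 points. In both cases the counted events suggest benefit where the total shows harm.

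**The case against.** The strongest reply is that the sentence is being read too narrowly. All potential events are to be recorded, any period of illness counts whatever its cause, hospitalized injuries count, and a study doctor and a safety monitor stand behind the process. Hotline staff join a weekly meeting that discusses adverse events (protocol amendments section), and participants may report later occurrences (ancillary and post-trial care). The article is also condensed, so event forms and symptom lists may sit in a fuller document.

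Much of this stands, and it rules out several stronger readings that a reader might infer:

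- That exercise injuries can never be counted. Hospitalized ones are counted, and some others can be read as illness.
- That the safety result is biased towards no difference. The article describes no between-arm safety analysis, none of the four primary domains is a safety domain, and step 4 shows that the error need not pull towards zero.
- That some 41,000 to 45,000 exercise performances measure missed harm. They measure maximum exposure.
- That the article states KOKU is used unsupervised in this trial. It says so of earlier studies ("motivating, and entertaining after 6 weeks of independent and unsupervised usage"). Here it is a reasonable inference from app use after an instruction visit.
- That distress from the daily health questions is a further gap. The article gives no basis for this, and questions can be skipped.

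The reply does not remove the core. The term is defined in the sentence after the recording rule, so the word potential adds no event types. If counting depends on whether each recorder regards a sore back as illness, the definition is not doing its job. Discontinuation reasons miss the injured participant who carries on. And the definition is not a detail left to another document: the article states it.

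**Conclusion.** The point holds as a badly fixed rule. Applied as written, the definition is likely to under-record non-fall injury, pain and dizziness in the full arm, which alone receives strength and balance training. The error leans towards missing harm there, and could make the arm look safer if falls decline.

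Its size cannot be established from the documents. Under the assumed rates, an excess shrinks in proportion to the share of injuries that happens to be counted, and it vanishes only if that share is zero. The conclusion rests on reading the list as closed, which its wording supports, and on KOKU having some excess of minor injuries, which is plausible but not quantified. Neither the sample size of 720 nor the efficacy analyses are affected. The change is worth making because it is cheap and because any safety statement depends on it.

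**What to change.** Which remedy applies depends on whether follow-up is still running. The trial status section gives 31 August 2024 as the end of recruitment, which puts the last six-month visits at around the end of February 2025, before Version 3 of 30 September 2025. The research ethics approval section still calls enrolment ongoing. On the recruitment dates, follow-up has probably ended.

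- **If any follow-up remains:** extend the definition to any injury, new or worsened pain, dizziness or musculoskeletal complaint, and apply it identically in all three arms.
- **If follow-up is complete:** code such events from records already held, for example documented reasons for deviation or discontinuation and any helpline or feedback-app entries. Report them as a non-comparative listing, since the feedback app exists only in arms 1 and 2 and collects app-use and usability feedback. Limit any comparative safety statement to illness, hospitalization and falls, and state that non-fall exercise injuries were not systematically collected.

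The cost is a reworded sentence, or a pass through existing logs. The downside is more minor events to log or code, and a less favourable count in the full arm. Retrospective coding will remain incomplete.
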